**Figure 3 figure3:**
[figure not shown]
Enrollment pathway of the Vientiane multigenerational birth cohort. VITERBI: Vientiane multigenerational birth cohort.

### Data Collection Instruments

The VITERBI study has a total of 6 questionnaires: (1) child enrolled during pregnancy (ie, index women), (2) child enrolled after birth (late enrollment), (3) postpartum form to collect birth outcomes, (4) adult questionnaire for the child’s father, grandparents, and great-grandparents, (5) a short questionnaire for family members who are incapacitated or have a cognitive impairment, and (6) household characteristics. Table 1 shows extensive information about the data collection instruments. All surveys are administered in-person via tablets by trained staff in the field and uploaded remotely to a web-based server at the end of the workday. Each questionnaire is briefly described below but can be accessed by reasonable request.

**Table 1 table1:** Data collection for each participant in the Vientiane multigenerational birth cohort (VITERBI).

Question type			Participants										
			Index mother		Late enrollment		Index mother postpartum		Adult^a^ (<60 years)		Adult^a^ (≥60 years) with no cognition problem		Adult^a^ (≥60 years) with cognition problem
Demographics			✓		✓				✓		✓		✓
Employment			✓		✓				✓		✓		
Obstetric history			✓		✓				✓^b^		✓^b^		
Antenatal care			✓		✓								
Prenatal supplementation			✓		✓								
Tobacco use			✓						✓		✓		
Alcohol consumption			✓						✓		✓		
General diet			✓						✓		✓		
Dietary salt			✓						✓		✓		
Handwashing practices			✓						✓		✓		
Raw food consumption			✓						✓		✓		
Physical activity			✓						✓		✓		
Transportation			✓						✓		✓		
Sedentary behavior			✓						✓		✓		
Pattern recognition and digit span			✓						✓		✓		
Disability			✓						✓		✓		
History of raised blood pressure			✓						✓		✓		
History of diabetes			✓						✓		✓		
History of raised cholesterol			✓						✓		✓		
History of cardiovascular disease			✓						✓		✓		
Experience of pain and arthritis			✓						✓		✓		
Chest pain			✓						✓		✓		
Cervical cancer screening			✓						✓^b^		✓^b^		
Health history			✓						✓		✓		
Environmental exposure			✓						✓		✓		
Family survival history			✓		✓				✓		✓		
Quality of life			✓						✓		✓		
Depression, anxiety, stress			✓						✓		✓		
Resilience			✓						✓		✓		
Recent birth outcomes					✓		✓						
Breastfeeding initiation, exclusivity, duration					✓		✓						
Postpartum depression					✓		✓						
Postpartum medical visit					✓		✓						
Instrumental Activities of Daily Living Scale											✓		✓
Activities of Daily Living													✓
Revised Hasegawa Dementia Scale											✓		✓
**Physical measurements**													
	Blood pressure	✓		✓		✓		✓		✓			
	Heart rate	✓		✓		✓		✓		✓			
	Weight	✓		✓		✓		✓		✓			
	Height	✓		✓		✓		✓		✓			
	Waist circumference	✓		✓		✓		✓		✓			
	Hip circumference	✓		✓		✓		✓		✓			
	Leg length	✓		✓		✓		✓		✓			
	Trunk length	✓		✓		✓		✓		✓			
	Mid-upper arm circumference	✓		✓		✓		✓		✓			
	Hemoglobin	✓		✓		✓		✓		✓			

^a^Relation to the child: father, grandmother, grandfather, great-grandmother, and great-grandfather.

^b^Women only.

### Index Women

Women enrolled during pregnancy were asked about their pre–pregnancy weight in kilograms, antenatal care, obstetric history, and plans for infant feeding. If enrollment occurred after birth, a shortened questionnaire was provided so as not to interfere with the mother-infant bonding (late enrollment questionnaire).

### Postpartum Interview

The postpartum questionnaire obtains information about the child’s birth outcome, health status, and general obstetric and postpartum experiences. Breastfeeding initiation and duration are assessed using questions from the Infant Feeding Practices Survey II [28]. Postpartum depression is assessed using the Edinburgh Postnatal Depression Scale [29]. Only when the women moved to a district outside the VITERBI catchment area were the questionnaires completed via telephone.

### All Adult Family Members

Utilizing validated questionnaires, we compiled an extensive interview to assess population characteristics. Each questionnaire includes the following information: demographic information; behavioral measurements for tobacco use, alcohol consumption, diet, and physical activity; health history; physical measurements, including blood pressure, height, weight, and waist circumference; sections from the WHO stepwise approach to surveillance [30]; hemoglobin levels by using the HemoCue Hb 301; family survival history; self-rated general quality of life [31]; environmental exposures to pesticides and cooking conditions; general mental health assessed using the Depression Anxiety Stress Scales [32,33]; cognitive status using progressive matrices [34] and the digit span [35]; and resilience levels [36]. Only women are asked the cervical cancer screening question from WHO stepwise approach to surveillance [30].

### Older Adults (Aged 60 Years or Older)

Individuals aged 60 years or older complete additional aging-related modules: Activities of Daily Living (ADL) and Instrumental Activities of Daily Living Scale are assessed using the Barthel [37] and Lawton [38] index, respectively. The Revised Hasegawa Dementia Scale [39] is used to assess cognitive impairment. If there is any indication that the adult is cognitively unable to complete the full-length interview, a short questionnaire only including these indicators was included. The main caretaker would answer questions regarding ADL. Only ADL was assessed among adults who had a main caretaker.

### Household Questionnaire

The Demographic and Health Surveys Phase 8 Questionnaire for household characteristics is used to assess access to drinking water, toilet facilities, mosquito net use, wealth and assets, food security, and use of social services.

### Retention of Participants

We collect a variety of contact information to reduce participant attrition. Participants provide their first and family names, address, phone number, email address, village leader name, temple or religious organization, and the contact information of a family member or close friend. In addition, we provide a small gift for participation. Immediately after the physical examination during baseline interview, all participants receive their biometric test results. Results include blood pressure, hemoglobin levels, and waist and hip circumference values. Results are explained during the session by licensed medical personnel (eg, staff nurses) and written on an information pamphlet for future reference. If the test results are abnormal, participants will be referred to their local health center for treatment. In addition, all participants who complete the baseline questionnaire receive a small gift (ie, hand soap) that equates to approximately US $1.

### Data Management

All questionnaires and data management are conducted in Open Data Kit (ODK). ODK is an open-source Android app that supports mobile data collection services. ODK Collect replaces paper forms used in survey-based data gathering and can be utilized without network connectivity. It supports a wide range of question types and answer formats. All data collection will occur offline on password-protected Android devices. Data connectivity will only be used to send data collected in the field at the end of the workday, when the data collection staff are in network range. Data storage is on a local secured server at Swiss Tropical and Public Health Institute by using the ODK Aggregate server.

### Statistical Analyses

The main goal of our study is to provide descriptive epidemiologic information on the current health status of a representative, purposive sample of children and their families in Vientiane province, Lao PDR. This includes incidence and prevalence estimates, geospatial maps displaying disease distributions, and factors of health and health behaviors (ie, accessing health care). Currently, no statistical analyses are planned. However, any additional research study will submit a separate institutional review board application.

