Our Vientiane multigenerational birth cohort (VITERBI) is the first multigenerational birth cohort created in the urban and semiurban districts of Vientiane capital, Lao PDR, focused on intergenerational health and life course trajectories of children, their parents, grandparents, and great-grandparents. Cohort data will be analyzed to quantify key health challenges and gaps across population groups, ultimately to develop interventions and social impact programs for the improvement of population health.

VITERBI has 3 main aims:

Establish a multigenerational birth cohort in Vientiane capital, Lao PDR, which is representative of the local population.Serve as the basis for additional observational (ie, cross-sectional) and intervention studies that promote population health in Vientiane province.Investigate the social, epidemiological, and medical problems of public health importance to Lao PDR, including intergenerational prevalence of overnutrition and undernutrition, access to antenatal care, adult access to health care, prevalence and predictors of communicable and noncommunicable diseases within families, the current status of geriatric care, and its socioeconomic determinants.

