## Methods

### Study Design

The VITERBI cohort will be established in the Vientiane capital of Lao PDR and is a prospective longitudinal birth cohort study enrolling children (during pregnancy), their parents, and relatives up to 3 generations (maternal and paternal grandparents and great-grandparents). Four districts of Vientiane capital were purposely selected based on overall socioeconomic status: Chanthabuly and Sikhottabong are 2 districts located in urban areas of high socioeconomic status, while Sangthong and Mayparkngum are 2 districts located in the semiurban, less developed areas of low socioeconomic status.

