Women who were not enrolled during pregnancy are enrolled postpartum to increase enrollment coverage. Birth records are obtained from central hospitals and local health centers to identify recent births that occurred within the cohort window. Staff attempt to contact these women who were neither enrolled nor declined a previous recruitment attempt during pregnancy. Study staff also obtain vaccination records from central health entities to cross-check infant enrollment with both on-time and postpartum recruitment and attempts to recruit women who do not appear in either channel (Figure 3). Access to these records is facilitated by the Lao Tropical and Public Health Institute through the Ministry of Health. Formal birth records obtained from hospitals and vaccination records from the National Immunization Program are used to evaluate recruitment rates. Increasing the overall enrollment coverage of eligible women (prepartum and postpartum) assures that the cohort represents the target population.

Index woman enrollment is the cornerstone for subsequent enrollment of the child’s relatives. In the field, VITERBI staff work closely with the index women to construct family trees detailing relatives of the child who are alive, eligible (living in the 4 study districts), and available to take part in the study. The family tree document guides staff recruitment efforts by providing basic demographic (name, age, and relationship to the child) and contact information of all family members who can be included. As we recruit additional family members, we anticipate their input will continue to guide recruitment and interview of subsequent members by reviewing the family tree document.

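### Representativeness is claimed for Vientiane province, but the cohort comes from four purposively chosen districts and the population it stands for is never defined

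*Protocol article*

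**What the plan says.** In the protocol article, aim 1 (Introduction, also in the Abstract) is to "Establish a multigenerational birth cohort in Vientiane capital, Lao PDR, which is representative of the local population". The local population is not defined.

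The Study Design section describes how the area was chosen: "Four districts of Vientiane capital were purposely selected based on overall socioeconomic status". Two of the four, Chanthabuly and Sikhottabong, are described as urban and of high status. The other two, Sangthong and Mayparkngum, are described as semiurban and of low status.

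The Statistical Analyses section then states the main goal for a wider area: "descriptive epidemiologic information on the current health status of a representative, purposive sample of children and their families in Vientiane province". Incidence and prevalence estimates and disease maps are listed under that goal. The same section says that no statistical analyses are planned at present.

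The Recruitment section describes an attempt to find every birth in a one-year window through several channels. It concludes: "Increasing the overall enrollment coverage of eligible women (prepartum and postpartum) assures that the cohort represents the target population". The check on this is that "Formal birth records obtained from hospitals and vaccination records from the National Immunization Program are used to evaluate recruitment rates".

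**The concern.** The same sample is called both representative and purposive, and the area it is said to represent changes between sections: local population, target population, Vientiane capital, Vientiane province. Choosing districts from two ends of a socioeconomic range is a sound way to obtain variety or contrast. It does not make their combined population a miniature of the province, because the mix of urban and semiurban families then depends on which districts were picked and how fully each was enrolled.

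Representativeness is aim 1, and incidence and prevalence estimates are the stated main goal. A reader who takes the wording at face value would treat a cohort estimate as a province estimate. Composition error does not fall as enrolment rises, so a large cohort could give an interval that is narrow and wrongly centred.

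**Working it through.** **Claim against design.** There is no derived figure to reproduce: the targets of 3000 children and about 13,000 people carry no precision, prevalence or power input. The first check is textual.

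- Area claimed: Vientiane province (Statistical Analyses); a local population in Vientiane capital (aim 1).
- Area sampled: four named districts, chosen on socioeconomic status (Study Design). Eligibility of index women is limited to these districts and the birth window (Participants), and relatives must also live there (Recruitment).
- Link between the two: no probability selection of districts, weighting or standardisation is described.

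Full coverage of the four districts supports inference to eligible families there. It gives no information about districts that were not chosen.

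**Coverage inside the four districts.** The document itself limits how much coverage can assure:

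- Women who plan to move away permanently, or who have a medical, intellectual or psychological disability, are excluded (Participants).
- Recruitment through two national hospitals brought in more women than recruitment at lower-level facilities (Discussion).
- Some women use private care or none, and the authors concede that some routes to eligible women probably remain unused (Discussion).
- Recruitment rates are judged against hospital birth records and immunisation records, which are also used to find women. A birth on neither list is missing from the denominator, so measured coverage can be too high.
- Older relatives enter only through a family with a birth in the window, and only if available.

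**Illustration of size.** Every prevalence and share below is an assumption; only n=3000 is from the document.

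*Sampling error*, treating the children as a simple random sample and ignoring clustering:

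- Standard error at p=0.30: √(0.30 × 0.70 / 3000) = 0.84 points.
- 95% half-width: 1.96 × 0.84 = 1.64 points. It is 1.07 points at p=0.10 and 1.79 at p=0.50.

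*Composition bias* of an unweighted estimate = error in semiurban share × urban-semiurban prevalence gap:

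| Share error | Gap 5 points | Gap 10 points | Gap 20 points |
|---|---|---|---|
| 10 points | 0.5 | 1.0 | 2.0 |
| 20 points | 1.0 | 2.0 | 4.0 |
| 30 points | 1.5 | 3.0 | 6.0 |

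At p=0.30 and n=3000, a bias of 0.5 points leaves a nominal 95% interval with about 91% coverage, and a bias of 2.0 points with about 33%.

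*Unsampled districts.* Bias = share of the population living in them × their difference in prevalence. With shares of 30% to 70% and differences of 2 to 10 points, it runs from 0.30 × 2 = 0.6 to 0.70 × 10 = 7.0 points. Coverage at p=0.30 then runs from 88.9% to about 0%.

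**The case against.** The strongest reply is that this is a matter of wording and that no biased estimate is actually planned. Much of it stands, and it rules out several stronger readings.

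- A reader might infer that pooled prevalence figures will be published for the province. The document does not say so: pooling is not mentioned, no analysis is currently planned, and the maps suggest some display by area. Weighting and variance methods may properly be left to a fuller plan, so their absence is no fault.
- A reader might infer that the Recruitment section claims coverage makes the cohort representative of the province. It does not name the province. It speaks of eligible women, which most naturally means women in the four districts, where an attempted census is relevant evidence. The fault there is an undefined target and the strength of the verb.
- A reader might conclude that the design does not sample the province's population at all. It samples part of it, with the intention of near-complete enrolment there.
- A reader might object that urbanicity and socioeconomic status coincide across only four districts. No contrast between district groups is planned, and household wealth is collected, so this does not count against the plan.

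It is also fair to say that village informants are used specifically to reach women outside the public care circuit, which reduces the number missed, and that the sizes above rest wholly on assumed values. None of this reconciles the provincial claim with the way the districts were chosen.

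**Conclusion.** The point holds as a mismatch between claim and design. The article claims representativeness for an area wider than its purposive four-district frame, names the population inconsistently, and overstates what coverage can assure within that frame.

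The consequence is conditional. If an unweighted province-wide estimate were produced, it would carry a bias that enrolment cannot remove. For an assumed 10-point share error this is small beside the 1.6-point half-width when the prevalence gap is 5 points, and larger than it when the gap is 20. The actual size cannot be known from the document. The textual conflict does not depend on these assumptions and should be corrected, because it governs what the study can conclude on aim 1 and its main goal.

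**What to change.** 1. Define the target population once, as eligible births in the window, and their resident relatives, in the four named districts. Use that definition in the Abstract, aim 1, Recruitment and Statistical Analyses.
2. Delete or qualify *representative* wherever it refers to Vientiane province or capital.
3. In Recruitment, replace the statement that coverage assures representation with coverage reported by district and recruitment channel, and say that births on neither the hospital nor the immunisation list are not counted.
4. Report estimates by district or by urban and semiurban stratum. Weight any four-district total by registered births divided by enrolled births in each district, from the records already obtained and provided that they show district of residence. State that these records may miss some births, and that such weights correct only for unequal coverage between the four districts.
5. Allow a province-wide figure only with external weights and a stated assumption about the unsampled districts.

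Items 1 and 2 are wording changes. Items 3 and 4 need counts by district and channel from records that the authors describe as disorganised and partly handwritten, so they take some staff time. The scientific cost is a narrower claim and slightly wider intervals.

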## Results

As of April 2024, this study has enrolled 3500 pregnant women and 4579 family members. Study participation is ongoing until May 2025 at minimum, with the goal to extend follow-up until 2050. The cohort has already served as a basis for additional observational and intervention studies that promote population health in Vientiane province: (1) VITERBI GUT, a prospective birth cohort studying the link between early life malnutrition, the microbiota, and metabolic health [5] and (2) a randomized controlled trial providing social transfers to increase exclusive breastfeeding and promote maternal and child health [40].

## Discussion

Multigenerational prebirth cohorts provide in-depth information about pregnancy, infants, early childhood, intergenerational health and wealth cycles, and etiology for specific diseases. Conducting longitudinal cohort studies in low-and middle-income countries provides unique challenges that are often not seen in high-income nations.

One key challenge in the specific context of Vientiane capital is the lack of robust information technology systems that would facilitate official data sharing and provide patients with personal records. Although decentralized operations might improve health system equity in hard-to-reach places subject to remote conditions and limited infrastructure, widespread deficiency of interfacility and interagency communication also results in fragmentation of the health system [41]. The VITERBI recruitment methodology employs diverse strategies in an attempt to reach eligible women and their families across different channels of the public health care and municipal systems. Of note, the recruitment efforts of women seeking and receiving care at 2 national facilities, Mother and Child Hospital and the maternity ward of Mahosot Hospital, yielded higher enrollment compared to province-level and district-level facilities. Face-to-face contact with local health staff and officials is an effective strategy for identifying eligible participants, as centralized data sharing and communication are not effective strategies in Lao PDR. Although record-keeping may vary between villages and districts, local staff generally have knowledge and records—both formal and informal—of pregnancies within their jurisdiction. Basing their work out of one of the study districts for prolonged periods, VITERBI staff are able to develop consistent partnerships with local staff at both the district and village levels. This strategy is particularly useful in recruiting women who may not be accessing health services within the previously described VITERBI contact circuit (eg, who are accessing private services or are not accessing any health care services).

Despite the varied and often fragmented channels for identifying and recruiting eligible participants, close collaboration with stakeholders at all levels, detailed study coordination from our team, and adaptive communication and working strategies have helped increased enrollment. Although there likely remains untapped avenues for reaching and recruiting eligible women, the previously described methods currently push the operational limits of our administrative and fieldwork staff. These staff members contend with the need for persistent communication with local health authorities, receive redundant and disorganized population data, and work around convoluted timelines set by administrative bottlenecks. These challenges emphasize the need to develop adaptable workflows with flexible coordination and strong collaboration among the staff.

Further challenges to producing a clean and robust database for a cohort of this magnitude include maintaining record completeness and reconciliation between the web-based questionnaire database and physical forms. When physical forms are collected (eg, participant consent forms, family trees) from the field, they are submitted biweekly to the main office to be double-checked and filed. This check is essential to ensure that no duplicate ID numbers have been assigned to different index women—an error that occurs due to misprinting of questionnaire codes associated with the IDs and the dissemination of misprinted forms to interview staff working in different groups in different areas of the same district. Duplicate ID numbers are detected by thorough check of the physical forms and then amended in the web-based database by manually assigning a new unique VITERBI ID in ODK.

All forms, including physical consent and contact forms alongside digital survey forms, must be checked for completeness. Then, physical and web-based forms must be compared with one another to ensure essential information (name, date of birth, contact phone number, district of residence, etc) match to the best of our ability. The Lao language and naming system presents unique challenges, as there is no standard Romanization, and often an individual is identified by an informal name that does not match legal or medical records. These factors result in multiple spellings of the same name in English translation and several names being associated with one individual. Often, informal names are quite generic, which can lead to confusion if there are no additional formal names or surnames listed for the participant. For this study, we collate all the records and associate as much identification information as is available with the unique VITERBI ID numbers. Thus, we rely on the index numbers to identify participants.

Many lessons learned from VITERBI can be used for other cohort studies in low-resource settings. These lessons include:

Local capacity building and continuous strengthening is essential. A thorough training of all research staff is critical for minimizing data collection errors. Creating sustainable institutional partnership for comparative cohorts of mutual benefit for different partners is also key for future research.Building trust with local leaders facilitates identification of participants and creates community ownership of the cohort goals.In minority populations such as the Hmong ethnic group in Vientiane, utilizing local staff that reflect the community population who act with high cultural competency from villages or neighborhoods is important for engaging difficult-to-reach populations.Flexibility and creativity in research staff are key. Participant identification is difficult, and the local study staff may need to adapt recruitment strategies in order to engage the population. Many of the villagers were only available in the evenings or on weekends, creating the need for staff to stay for long periods of time within the community.Study instruments need to be reflected across many different age and ethnic groups. The multigenerational aspect of the cohort calls for a multidisciplinary team to ensure cohesion across study questions.The medical system is overburdened, and medical records are not digitized. Collecting handwritten ledgers to identify and track children and their mothers is time-intensive and requires a formal data tracking system.

Each community offers unique challenges. In low-resource settings where longitudinal studies are more difficult, such data would often be the most beneficial for population health. For this exact reason, additional longitudinal studies should be conducted in these settings. Although the researcher should not be complacent in recognizing the specificity of the study setting, the methods and lessons described here may prove relevant in the formation of future studies in the Lao PDR context and beyond.

